### Analysis

Analysis will compare two groups of randomized patients, allocated in TXA group or placebo group on an intention-to-treat basis, regardless of treatment received, and outcomes will be presented as appropriate effect estimates and 95% confidence intervals.

In analysis of primary outcome, TXA and placebo groups will be compared regarding the TGA parameter, ETP of baseline and follow up values. The same analysis will be performed for secondary outcomes such as platelet function (ADPtest and TRAPtest), coagulation factors (FV; FVIII; vWF, Fibrinogen and D-Dimer) and other TGA parameters (LT, TtP, and Ph). A subgroup analysis for primary outcome will be based on main risk factors for PPH, such as uterine atony, placental factors and genital trauma.

A detailed statistical analysis plan (SAP) will be finalized prior to the sub-study unblinding for final analysis. All statistical analysis will be conducted with R and STATA statistical package.

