### Outcomes

***Measures of the primary and secondary outcomes of ETAPlaT study.*** The primary outcome will be the effect of TXA on thrombin generation [thrombin generation assay (TGA) parameter – endogenous thrombin potential (ETP)]. Secondary outcomes will include the effect of TXA on platelet function (Multiplate® tests: ADPtest and TRAPtest), fibrinogen, D-dimer and FV, FVIII, vWF levels, and other TGA parameters [lag time (LT); time to peak (TtP); and peak height (Ph)]. Levels of all parameters will be assessed on two venous blood samples, collected at the baseline and between 30±15 minutes after the first dose of study treatment is given.

Further secondary outcomes will include assessment of the relationship between these parameters, patient demographics and clinical data (in the time frame from randomization to the patient discharge from the hospital or until 42 days).

***Outcomes of the main study WOMAN trial.*** The WOMAN trial will not provide information about platelet function, thrombin generation, fibrinogen, D-dimers and coagulation factors V, VIII and vWF in patients receiving TXA/placebo. However, the most reliable estimates of the effects of TXA on the outcomes for women with PPH will be provided by the WOMAN trial.

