### Sample size

We aim to assess if TXA, when compared to a placebo, has an effect on change over time on the TGA parameter, ETP. Therefore, the sample size calculation is based on this parameter. Patients are expected to be equally allocated between the two intervention groups; 88 patients per group (total, 176 patients) are needed to detect the difference of ETP 243nM/min, with a change between the groups at a 5% significance level with a power of 80%.

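### The Analysis section's description of the primary ETP comparison names no baseline-adjusted estimator and fits the change-based sample size on only one reading; ANCOVA on baseline ETP would be a free gain in precision

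*Protocol article*

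**What the plan says.** **Sample size.** The aim is to learn whether TXA "has an effect on change over time on the TGA parameter, ETP. Therefore, the sample size calculation is based on this parameter". The result is that "88 patients per group (total, 176 patients) are needed to detect the difference of ETP 243nM/min", at 5% significance and 80% power. No SD, no correlation and no sidedness is given.

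**Outcomes.** "Levels of all parameters will be assessed on two venous blood samples", one at baseline and one at 30±15 minutes after the first dose. Under the section on procedures, the first sample is drawn after randomisation and before that dose.

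**Analysis.** "In analysis of primary outcome, TXA and placebo groups will be compared regarding the TGA parameter, ETP of baseline and follow up values". That comparison is then repeated for ADPtest, TRAPtest, FV, FVIII, vWF, fibrinogen, D-dimer, lag time, time to peak and peak height, which makes ten secondary laboratory outcomes. Results are to be given as suitable effect estimates with 95% confidence intervals, and a detailed SAP is to be completed before unblinding.

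**The concern.** Every woman is due to have a pre-dose and a post-dose ETP. In a randomised trial of that form there are three usual ways to compare the arms: follow-up values alone, change from baseline, or follow-up adjusted for baseline. They have different standard errors and respond differently to a chance difference between the arms at baseline. The Analysis sentence mentions both values but does not say how they are combined, and its wording differs from that of the Sample size section.

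If the sentence means a comparison at each time point, the baseline half tests a null hypothesis that randomisation already makes true. The follow-up half sets aside a measured predictor of the outcome and is not the quantity on which the trial was sized. If it means a change score, it fits the sizing but gives up some precision. The protocol itself lists the small number of patients as a limitation, and the same comparison is repeated for ten further outcomes, so the choice matters.

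**Working it through.** **Inputs.** From the Sample size section: 88 per group, difference 243, 5% significance, 80% power. Assumed because not stated: two-sided test, equal variances at the two times and in the two arms, and r between 0.3 and 0.9. All results use the normal approximation.

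**The plan's own figure.** With no SD stated, 88 per group cannot be reproduced independently. It can only be solved backwards:

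SD = 243 × √(88/2) / (1.960 + 0.842) ≈ 575, a standardised difference of 0.42.

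Putting 575 back in returns 88 per group and 80.0% power. That is circular and confirms nothing about the SD.

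**Variances.** With s the SD of a single ETP measurement:

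- follow-up only: s²
- change score: 2s²(1 − r)
- ANCOVA: s²(1 − r²)

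So the ANCOVA variance is (1 + r)/2 times the change-score variance and (1 − r²) times the follow-up-only variance. Neither ratio exceeds 1 for r between 0 and 1.

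**Power if 575 is the SD of change** (the reading that fits the Sample size wording). Example at r = 0.5: adjusted SD = 575.3 × √0.75 = 498.3; SE = 498.3 × √(2/88) = 75.1; 243/75.1 = 3.235; 3.235 − 1.960 = 1.275; power 89.9%.

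| r | Change score | Follow-up only | ANCOVA |
|---|---|---|---|
| 0.3 | 80.0% | 91.2% | 93.5% |
| 0.5 | 80.0% | 80.0% | 89.9% |
| 0.7 | 80.0% | 58.3% | 86.0% |
| 0.9 | 80.0% | 24.0% | 82.0% |

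The 95% confidence half-width for the change score is 1.96 × 575.3 × √(2/88) = 170. Multiplied by √((1 + r)/2), it becomes about 137, 147, 157 and 166 for ANCOVA at the four values of r.

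**Power if 575 is the SD of a single ETP.**

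| r | Change score | Follow-up only | ANCOVA |
|---|---|---|---|
| 0.3 | 65.8% | 80.0% | 83.6% |
| 0.5 | 80.0% | 80.0% | 89.9% |
| 0.7 | 95.1% | 80.0% | 97.5% |

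**Chance imbalance.** The SE of the baseline difference is √(2/88) = 0.15 SD, a 95% range of ±0.30 SD. An imbalance of 0.30 SD shifts the follow-up-only estimate by r × 0.30 and the change score by (1 − r) × 0.30 in the opposite direction. At r = 0.7 these are 0.21 and 0.09 SD; at r = 0.3 they are 0.09 and 0.21 SD. If 575 is the single-measurement SD, 0.21 SD is half the target of 0.42 SD. These shifts average to zero over randomisations. ANCOVA removes the imbalance in the trial actually run.

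**The case against.** A reader might infer that the trial will be analysed without adjusting for baseline and so wastes power. The document does not support that. The Analysis sentence brings baseline values into the comparison, names no estimator and excludes no covariate. The covariates of a primary model are ordinary SAP content, and that SAP is not shown, so their absence here is not in itself a fault.

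A reader might also infer that the Analysis and Sample size sections contradict each other. They need not: comparing the arms on baseline and follow-up values can be a loose way of saying that change is compared. On that reading, with 575 as the SD of change, the trial keeps exactly its planned 80% power. Change-score and follow-up-only comparisons are both unbiased under randomisation, so ANCOVA would improve on a valid analysis rather than repair an invalid one.

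The size of any gain rests on an SD solved from the sample size and on a correlation that is nowhere given. A follow-up-only analysis would not always lose power: if 575 is the SD of change, it falls below 80% only when r exceeds 0.5. Nor can fewer women be recruited, because the Trial status section reports follow-up complete.

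All of this stands. What remains is that neither natural reading of the printed sentence (change, or separate time points) is the most precise use of data already collected.

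**Conclusion.** The point holds as a free improvement, not as an error in a stated figure. The Analysis section leaves the primary ETP contrast open to two natural readings. One agrees with the sizing and is valid but less precise than ANCOVA. The other departs from the sizing and leaves chance imbalance in the follow-up estimate, without bias on average.

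Against the change-score reading, ANCOVA lifts power from 80% by about 13.5 points at r = 0.3, falling to about 2 points at r = 0.9. This assumes a two-sided test, equal variances, and that the implied 575 is the SD of change. If 575 is instead the SD of a single measurement, the planned 80% belongs to the follow-up-only comparison, and ANCOVA gives 83.6% to 97.5% for r from 0.3 to 0.7. The direction does not depend on r under these assumptions; the size does. Whether the SAP already specifies baseline adjustment cannot be told from the article.

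**What to change.** In the SAP, before unblinding, state: the primary estimate is the TXA-minus-placebo difference in follow-up ETP from a linear model with treatment and baseline ETP as covariates, reported with its 95% confidence interval. Describe baseline values by arm without testing them. Use the same model for each of the ten secondary laboratory outcomes, with that outcome's own baseline as covariate.

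This stays in line with the change-based aim: in a linear model that includes baseline, the treatment coefficient is the same whether the outcome is follow-up ETP or change in ETP, so the target difference of 243 keeps its meaning.

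The cost is one or two sentences. The baseline samples are already part of the design, and no extra patients, samples or assays are needed. Recruitment has ended, so the analysis is the remaining place to gain precision. If the SAP already contains this model, confirming that closes the point.

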### Limitations of the study

One limitation of this sub-study is the small number of the patients that will be recruited. Another potential limitation is withdrawal of participation by patients from this study, or risk of loss of contact in case of complications after discharge from the hospital and within the period of 42 days after the birth.

### Trial Steering Committee (TSC) and Data Monitoring Committee (DSC)

A TSC for the WOMAN trial is in place and agreed to the conduct of this sub-study. Decisions of the TSC can influence immediately on the continuation of the WOMAN‐ETAPlaT study. Information about the WOMAN‐ETAPlaT study will be reported routinely to the TSC by [name]. An independent DMC is already in place for the WOMAN trial. Adverse events, which occur during the study period and are related directly to the WOMAN‐ETAPlaT study, will be reported to the DMC.

The sub-study had its responsibilities coordinated by the TCC, which may attribute responsibilities to third parties, and will be detailed by suitable arrangements.

### Trial status

Recruitment for the WOMAN ETAPlaT sub-study started on November 2013 and the final participant follow-up was completed in March 2015. Data cleaning is ongoing.
